### Strategies to improve adherence to interventions {11c}

Every participant will receive a follow-up phone call from a research member at weeks 1 (t1), 3 (t2), 5 (t4), 9 (t5), and 13 (t6) to control for treatment adherence. In addition, the exercise program will be graphically presented in a paper sheet (control group), or using audio-visual methods (CareHand group) with explanations to encourage adherence to treatment. Participants using the CareHand app will have access to relevant information, previously described, e.g., self-management strategies to deal with pain and fatigue and enhance performance in daily live activities, and dietary advices, among others, to encourage participants to continue with the proposed protocol.

### Relevant concomitant care permitted or prohibited during the trial {11d}

Participants will not be allowed to receive other manual therapy interventions or participate in other trials during the study period.

Medical stable treatment, using DMARDs, will be permitted throughout the study period. Pharmacological management of RA with DMARDs is very common, and its potential effects may increase when combined with exercise programs [20].

### Provisions for post-trial care {30}

Hand exercise programs are safe. In patients with RA, no adverse effects have been attributed to self-management with hand exercises [16]. Hence, no harm or adverse effects are expected from trial participation. Nonetheless, participants will be asked to report any possible side adverse effect.

### Outcomes {12}

#### Primary outcomes

The primary outcome is hand performance in different domains, as assessed with the Michigan Hand Outcome Questionnaire (MHQ). The MHQ is a well-established and commonly used tool for patients with RA and consists of six subscales that evaluate overall hand function, daily life activities, work performance, self-reported pain, esthetics, and satisfaction [29]. The final score ranges from 0 to 100, with higher scores indicating better performance, except for the pain domain, where higher scores represent more pain [30]. The MHQ has proven to be valid, reliable, and sensitive for people with hand RA, with good test-retest reliability (*r* = 0.66) and acceptable to excellent internal consistency (*α* = 0.66–0.90) [31]. In people with RA, the minimum clinically important difference (MCID) for the MHQ ranges from 3 (daily life activities) to 13 points (overall function) [32]. The validated Spanish version of the MHQ will be used in our study [33]. The MHQ will be collected at baseline (t0) and at 3 months (t7) from baseline.

#### Secondary outcomes

Secondary outcomes included self-reported pain intensity and morning stiffness, pain-free maximum grip and pinch force, and self-reported functional ability. Using a 0 to 10 VAS [34], where 0 denotes “no pain/no morning stiffness” and 10 denotes “the worst imaginable pain/morning stiffness,” participants will be told to report their average hand pain intensity and morning stiffness within the previous week. The VAS presents a good test-retest reliability (*r* = 0.94) [35] and is able to detect clinically relevant effects after intervention in people with different hand disorders [36]. The MCID for the VAS assessing pain intensity has been estimated at 1.1 points in patients with RA [37]. Self-reported pain intensity will be assessed at baseline (t0), and at 1 month (t3) and 3 months (t7) after baseline, whereas self-reported morning stiffness will be collected at baseline (t0), and at 3 months (t7) after baseline.

Handgrip strength is defined as the power of the hand muscles required in grasping or gripping, and can be divided in power grip (all the hand involved) or precision grip (only use of thumb and fingertips) [38]. A hydraulic hand dynamometer (Saehan SH5001, Saehan Corp., Masea, South Korea) will be used to evaluate power grip, following the guidelines of the American Society of Hand Therapy. The subject is seated, with the shoulder along the body and with no rotation, 90° elbow flexion, neutral forearm position, and the wrist with a “subtle” dorsal flexion (0–30°) [39]. Participants will be encouraged to grasp strongly without feeling pain or discomfort [39]. In patients with hand RA, a single trial is recommended to avoid discomfort and burden from subsequent measures [40]. The threshold for the MCID for power grip is estimated between 5 and 6 kg [41]. As regards precision grip, a pinch gauge (30 Lb. Mechanical Pinch Gauge, Baseline, USA) will be used. Following the same instructions, participants will be asked to hold the device between the index and middle fingers on one side and the thumb on the other side to evaluate the maximum pain-free pinch force [38]. Interrater reliability has shown to be almost perfect, with most ICC values over 0.97 [38]. A single measurement will be requested due to possible patient discomfort [42]. Handgrip and pinch strength will be assessed at baseline (t0) and at 3 months (t7) after baseline.

The self-reported functional ability will be evaluated by means of the shortened Disabilities of the Arm, Shoulder and Hand (DASH) questionnaire (*Quick* DASH). The *Quick* DASH questionnaire consists of 11 items scored on a 5-point Likert scale, resulting in a final score between 0 and 100 points, with higher values indicating more disability [43]. This tool includes two optional scales (work/music) which are not commonly collected [44]. The *Quick* DASH has shown to be highly reliable, internally consistent [45], and with good validity [46] and correlation with disease activity [43] in patients with RA. The test-retest and cross-sectional reliability and discriminant ability of this tool are similar to original DASH questionnaire [47]. The validated Spanish version of the questionnaire will be used [48]. The Quick DASH questionnaire will be collected at baseline (t0), and at 1 month (t3) and 3 months (t7) after baseline.

### Participant timeline {13}

A schematic diagram for participant timeline is shown in Fig. 3.

**Fig. 3 Fig3:**
[figure not shown]
Standard Protocol Items Recommendation for Interventional Trials (SPIRIT) figure

### Sample size {14}

Sample size estimation was based on detecting a mean between-group difference (CareHand vs. conventional) in the changes across the assessment points (baseline vs. after training, and baseline vs. 3-month follow-up) higher than 13 points for the overall MHQ, established as the clinically relevant threshold for this scale [49]. Assuming a two-tailed hypothesis, an alpha value of 0.05, and a desired power of 80%, 24 participants are needed per group to complete the study (Granmo Software, version 7.12, Institut Municipal d’Investigació Mèdica, Barcelona, Spain). To allow a 10% dropout rate, we will initially recruit at least 58 participants.

### Recruitment {15}

All possible eligible patients will be contacted directly via telephone to inform them about the aims and potential benefits of the study. Participants will be selected from the database of the Northern Seville and Aljarafe Health District, Andalusian Health Service, Seville, Spain. This Health District comprises 88 healthcare centers. For checking the recruitment viability, a query to this database was performed to confirm the number of patients diagnosed with RA. The search obtained 407 patients with hand RA as suitable for initial screening.

## Assignment of interventions: allocation

### Sequence generation {16a}

Using computer-generated random numbers in permuted blocks produced with an external website, all participants will be randomly assigned (1:1 ratio) to one of the study groups during baseline assessment, and after they have agreed to enroll in the study and signed the informed consent.

### Concealment mechanism {16b}

Sealed opaque envelopes will be used to conceal the treatment order allocation.

### Implementation {16c}

An external assistant will generate the random sequence. The principal investigator ([name]) will enroll participants and randomly assign them to one of the study groups.

## Assignment of interventions: blinding

### Who will be blinded {17a}

Outcome assessors and data analysts will remain blinded to participants’ allocation group.

### Procedure for unblinding if needed {17b}

The study lead investigator, the researcher in charge of explaining and delivering interventions, and the participants will not be blinded to the group allocation.

## Data collection and management

### Plans for assessment and collection of outcomes {18a}

Assessors will participate in a training session where they will be instructed in each measurement tool and clinical questionnaire to be used. Any doubt will be resolved, and one training data collection session will be conducted. Due to the common discomfort of patients with hand RA, only one trial for strength measures will be performed [40].

All participants will be assessed three times during the study: at baseline, and at 1 month (t3) and 3 months (t7) from baseline. Baseline measurements (t0) will be completed before randomization. Assessment at 1 month will be carried out with a phone call, and data of self-reported pain intensity (VAS) and the Quick DASH questionnaire will be evaluated. Data collection at baseline and at 3-month follow-up will be conducted in the public healthcare centers and will involve all outcome measures.

The MHQ, as the primary outcome, is a reliable, valid, and sensible questionnaire, with acceptable to excellent internal consistency (*α* = 0.66–0.90), and good test-retest reliability (*r* = 0.66) [31]. Construct validity obtained the highest results between overall hand function and activities of daily living (*r* = 0.83), and between satisfaction, overall hand function, and activities of daily living (*r* = 0.81–0.83) [31]. In people with RA, the MCID for the overall hand function is at 13 points [32]. As regards secondary outcomes, the VAS is a valid tool to evaluate pain intensity in chronic conditions, with a good test-retest reliability (*r* = 0.94). The MCID for the VAS is established at 1.1 points in RA patients [37]. The use of a hand dynamometer to assess grip strength is common for people with upper limb chronic disorders. This tool shows high interrater reliability (ICC = 0.93) [41], with a clinically relevant threshold that ranges between 5 and 6 kg [39]. For pinch grip force, the proposed assessment protocol has shown to be excellent (ICC > 0.97) [39]. Finally, the Quick DASH is a valid, reliable, and consistent tool [45, 46], with a similar test-retest reliability and discriminant ability to that of the DASH questionnaire [47].

### Plans to promote participant retention and complete follow-up {18b}

Participants will receive a phone call from a research member at weeks 1 (t1), 3 (t2), 5 (t4), 9 (t5), and 13 (t6) for improving their participation and adherence to intervention. These phone calls are aimed to resolve doubts, problems, or misunderstandings with their intervention protocol and to encourage patients to continue working.

Additionally, participants using the CareHand app will benefit from additional methods to promote self-monitoring and self-management. The hand RA-related information included in the app may also help to encourage participants to complete the study, as this includes the possible benefits associated with regular physical activity.

### Data management {19}

Participants’ personal information will be assigned a unique study identification code that will be stored in a password-protected database accessible only to the principal investigator. Study data will be entered in a different computer and linked to the participants ID. A member of the researcher team will double-check the entered data for accuracy.

### Confidentiality {27}

Shared data between members of the research team will be included in a password-protected Excel file and only linked to the participants ID to respect confidentiality.

### Plans for collection, laboratory evaluation, and storage of biological specimens for genetic or molecular analysis in this trial/future use {33}

This trial does not involve collecting biological specimens for storage. Hence, there are no plans for collection, laboratory evaluation, or storage of biological specimens for genetic or molecular analysis during the present trial.

## Statistical methods

### Statistical methods for primary and secondary outcomes {20a}

The statistical processing will be performed with the PASW Advanced Statistics (SPSS Inc., Chicago, IL), version 24.0, and according to an intention-to-treat principle. Data will be reported as mean, standard deviation, and confidence intervals (95% CI) or in percentage frequencies. The Shapiro-Wilk test will evaluate the normal distribution of the variables. The between-group differences in the mean changes of the outcome measures after intervention will be calculated using repeated-measures mixed models with patients as random effect, and group (conventional or CareHand) and time (baseline, 1 month, and 3 months) as fixed effects, and with adjustments for baseline imbalance. The Spearman rank test or Pearson product-moment correlation coefficient analysis may be used to analyze the associations between clinical data and mean changes in the outcome measures. Statistical significance is set at a *p* value < 0.05.

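### The listed primary model has no group-by-time term, so fitted literally its group coefficient would be half the 3-month MHQ effect and not the difference in change that the plan targets

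*Protocol article*

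**What the plan says.** All references are to the protocol article.

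- **Target.** Under Statistical methods {20a}: "The between-group differences in the mean changes of the outcome measures after intervention will be calculated using repeated-measures mixed models".
- **Model terms.** The same sentence specifies "repeated-measures mixed models with patients as random effect", then "group (conventional or CareHand) and time (baseline, 1 month, and 3 months) as fixed effects", and ends "with adjustments for baseline imbalance". It names no interaction and no contrast, and does not say how the baseline adjustment is made.
- **Powered quantity.** Sample size {14} is built on a "mean between-group difference (CareHand vs. conventional) in the changes across the assessment points", with the difference set as "higher than 13 points for the overall MHQ". It uses two-sided alpha 0.05, 80% power and 24 completers per group.
- **Timing of the primary outcome.** Under Primary outcomes: "The MHQ will be collected at baseline (t0) and at 3 months (t7) from baseline". For the MHQ the time factor therefore has two levels, not three.
- **Timing of baseline.** Under Plans for assessment {18a}: "Baseline measurements (t0) will be completed before randomization".

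**The concern.** Because baseline is a level of the time factor, baseline scores are responses in the model. A model with group and time alone then imposes one constant gap between the arms at every visit, including baseline, where randomisation makes the expected gap zero. The fitted difference in change is zero by construction, so the stated target is not a parameter of the listed model. What that model does return, the group coefficient, averages the null baseline gap with the follow-up effect.

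The estimate of the single primary outcome is at stake. A trial that achieved exactly the 13 points it calls clinically relevant could report about half of that and be read as falling short of its own threshold. The text also leaves open whether the primary result is the group coefficient, the interaction or a baseline-adjusted 3-month comparison. These give different estimates and can give different p-values.

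**Working it through.** **Inputs from the document:** difference in change d = 13; two-sided alpha 0.05; power 80%; 24 completers per group; 1:1 allocation; MHQ at baseline and 3 months; baseline measured before randomisation.

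**Assumptions (not in the document for this purpose):** an SD of change, since none is stated; a baseline-to-3-month correlation r from 0.3 to 0.8, with 0.66 as one value. The article gives 0.66 as the MHQ's test-retest reliability, which is not a 3-month correlation under treatment.

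**1. The plan's own sample size.** n per group = 2 × SD² × (1.96 + 0.84)² / 13². Solving backwards, 24 per group needs an SD of change of about 15.7 to 16.1. SD 16 gives 23.8, hence 24; SD 14 would need 19 and SD 20 would need 38. SD 16 is used below.

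**2. What the listed terms estimate.** Write the mean as μ + β·group + τ(time), with a patient random intercept.
- The group gap is β at every visit, so the modelled difference in change is β − β = 0.
- With complete data, the estimate of β is the unweighted mean of the observed group gaps over the visits.
- MHQ: (0 + d)/2 = 13/2 = 6.5. Simulation (24 per arm, 150 runs per setting) gave 6.5 and 6.3.
- With the group-by-time term added, simulation recovered 12.5 to 13.5. ANCOVA at 3 months gave 12.7 to 13.3.

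**3. If baseline is also a covariate.** Suppose y3 = a + d·group + c·y0 + e. The patient mean of the two responses is then (y0 + y3)/2 = a/2 + (d/2)·group + ((1 + c)/2)·y0 + e/2. The group coefficient is still d/2 = 6.5 (simulated 6.3 and 6.7). Its standard error is also half that of ANCOVA, so in this patient-mean regression the t statistic equals that of the 3-month ANCOVA.

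**4. Outcomes measured three times (pain VAS, Quick DASH).** The coefficient is (0 + d1 + d3)/3.
- If d1 = d3, it is two thirds of d3 (simulated 8.8 for a nominal 13).
- If d1 is half of d3, it is one half (simulated 6.6).

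**5. Power, with baseline not also a covariate.** Single-visit SD σ = 16/√(2(1 − r)); SD of the patient mean = σ√((1 + r)/2); contrast 6.5; standard error = SD × √(2/24).

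| r | σ | SD of patient mean | Power of group main effect (t to normal) |
|---|---|---|---|
| 0.3 | 13.5 | 10.9 | 52–54% |
| 0.5 | 16.0 | 13.9 | 36–37% |
| 0.66 | 19.4 | 17.7 | 24–25% |
| 0.8 | 25.3 | 24.0 | about 15% |

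The interaction contrast has 79% (t) to 80% (normal) power at SD 16.

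**6. Power, with baseline also a covariate.** By step 3 the test matches ANCOVA. At r = 0.66 the ANCOVA residual SD is 19.4 × √(1 − 0.66²) = 14.6. The standardised effect is 13/(14.6 × √(2/24)) = 3.1, so power is about 86–87%. Direct mixed-model fits kept about 80%, but many gave convergence or boundary warnings, so that figure is approximate. The loss in step 5 therefore does not arise here, although the estimate is still halved.

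**The case against.** The strongest reply is that the same sentence names the difference in mean changes as what the model will deliver. With baseline among the times, only the interaction can deliver it, so an analyst who takes the target seriously must add the term. The text never says main effects only and never makes the group coefficient the test. Group and time may simply be a list of factors, shortened for a journal article whose fuller protocol or analysis plan is not shown. This stands to the extent that the halving is conditional on a literal fit. It does not remove the point: the article chose to state the terms of its primary model, and those terms do not contain its stated target.

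A reader might go further and infer that the trial will report half its effect and will usually miss a true 13-point difference, with power near 24%. The documents do not support that. The halving needs a literal fit with the group coefficient reported. The power loss also needs the clause on baseline imbalance to be ignored, because a baseline covariate keeps power near 80% or above. The 24% further rests on an SD that can only be back-solved from the sample size, and on a reliability coefficient used as a longitudinal correlation.

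Nor does that clause repair the model. Its form is not given, and in its most natural form, baseline as a covariate, the coefficient stays at 6.5.

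**Conclusion.** The point holds in conditional form. The listed fixed effects do not include the term that carries the stated target. If they are fitted literally and the group coefficient is reported, the primary estimate is half the 3-month effect: 6.5 for a true 13, with or without a baseline covariate. That result needs only a zero expected baseline gap and complete data at two visits. For pain VAS and Quick DASH the fraction depends on the unknown 1-month effect and is two thirds if the two effects are equal.

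The fall in power to roughly 15%–54% is a secondary and weaker consequence. It applies only without a baseline covariate and under the assumed SD of 16 and correlations of 0.8 to 0.3. The document does not show that the authors intend the additive model. It does leave the primary contrast open and lists terms that point to the wrong one.

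**What to change.** Replace the model sentence with one of the following, chosen before unblinding:

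- **Baseline as response.** Fixed effects group, time and group-by-time, with patient as random effect. The primary contrast is the group difference in MHQ change from baseline to 3 months, with its 95% CI. This matches the quantity on which the sample size is built.
- **Baseline as covariate.** ANCOVA of the 3-month MHQ on group and baseline MHQ, reporting the adjusted group difference with its 95% CI. For pain VAS and Quick DASH, use only the 1-month and 3-month values as responses, with baseline as covariate, and name the 3-month group difference as the contrast.

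In either case, say what the adjustment for baseline imbalance consists of, and do not enter baseline both as a response level and as a covariate. State that the MHQ model has two time levels. The cost is a sentence or two in the analysis section, with no new data, visits or participants.

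### Baseline adjustment is tied to imbalance instead of being fixed in advance, so the primary MHQ comparison is in effect a change-score analysis and gives up precision that ANCOVA would keep

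*Protocol article*

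**What the plan says.** The section on statistical methods for primary and secondary outcomes ({20a}) sets the target as the between-group difference in mean change. The model is a repeated-measures mixed model with patient as random effect and with group and time as fixed effects. Time has three levels, the first of which is baseline, and the model is fitted "and with adjustments for baseline imbalance". The section does not name the adjusted variables, define imbalance, say whether adjustment always takes place, or constrain the groups to a common baseline mean.

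The sample size section ({14}) has the same target, a "mean between-group difference (CareHand vs. conventional) in the changes across the assessment points", and is powered for a difference "higher than 13 points for the overall MHQ". It concludes that "24 participants are needed per group to complete the study". It gives neither a standard deviation nor a correlation.

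The outcomes section ({12}) schedules the MHQ at baseline and 3 months only. The sole correlation quoted for the MHQ is its reliability, "with good test-retest reliability (*r* = 0.66".

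**The concern.** In a randomised trial any baseline imbalance is due to chance. The reason to adjust for baseline is that it predicts the outcome, and this is known before anyone is randomised. Making imbalance the ground for adjustment has two consequences.

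- **Precision.** With two MHQ measurements and free baseline means in each group, the group-by-time contrast is the difference in mean change. That is less precise than ANCOVA whenever the baseline to follow-up correlation is below 1. With 24 completers per group there is little precision to spare.
- **An open choice.** If adjustment may or may not be made, or may take different forms, depending on how the groups look, the primary p-value depends on a decision that the text does not settle.

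**Working it through.** **Inputs from the protocol article ({14}).** "Assuming a two-tailed hypothesis", "an alpha value of 0.05", power of 80%, a 13-point difference and 24 completers per group.

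**Assumptions.** The SD of change is not stated and is solved for below. The baseline to follow-up correlation r is not stated either; 0.66 is the MHQ test-retest value used as a stand-in, with a range of 0.3 to 0.9.

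**1. The plan's own figure.** The normal-approximation formula is n per group = 2(1.960 + 0.842)² SD² / 13². With SD = 16 this gives 2 × 7.849 × 256 / 169 = 23.8, so 24. Conversely, 24 per group with exactly 80% power implies SD = 16.07 (normal approximation) or about 15.7 (t distribution). So 24 cannot be reproduced from the article alone, but it fits a change SD of about 16. At SD 16 and 24 per group, power is 80.4% by the normal approximation and 78.7% by the non-central t.

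**2. What the planned model estimates for the MHQ.** With two time points and unconstrained means, the group-by-time term is (mean change, app) − (mean change, paper). A patient's baseline value is the same at both of that patient's time points, so as a covariate it cancels from this within-patient contrast. In 300 simulated trials (true effect 13) the group-by-time estimate had mean 13.19 and SD 4.48 both with and without the covariate. The rejection rates were 83.3% and 80.7%. Because the estimates have the same mean and spread, that gap does not show a gain in precision.

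**3. Variance against ANCOVA.** With a common SD s at both visits:

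- change score: 2(1 − r)s²
- ANCOVA: (1 − r²)s²
- ratio: (1 + r)/2, which is 0.83 at r = 0.66

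The effective SD falls from 16 to 16 × √0.83 = 14.6. Put another way, 24 per group performs like 24 / 0.83 = 28.9.

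**4. Power at 24 per group** (normal approximation, change SD held at 16.07 so that the change score has 80.0%):

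| r | variance ratio | ANCOVA power | gain (points) | n per group for 80% |
|---|---|---|---|---|
| 0.3 | 0.65 | 93.5% | 13.5 | 16 |
| 0.5 | 0.75 | 89.9% | 9.9 | 18 |
| 0.66 | 0.83 | 86.8% | 6.8 | 20 |
| 0.8 | 0.90 | 84.0% | 4.0 | 22 |
| 0.9 | 0.95 | 82.0% | 2.0 | 23 |

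On the t distribution at r = 0.66 and SD 16, power goes from 78.7% to 85.6%. Simulation with 60,000 trials per setting, which also bears the cost of estimating the baseline slope, gives:

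| r | change score | ANCOVA | ANCOVA only if baseline p < 0.05 |
|---|---|---|---|
| 0.5 | 78.6% | 88.1% | 79.4% |
| 0.66 | 78.3% | 84.5% | 78.8% |
| 0.8 | 78.1% | 81.4% | 78.3% |

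**5. Type I error of the open choice** (same simulation, no true effect, r = 0.66). Change score alone 5.1%, ANCOVA alone 5.1%, the strict p < 0.05 imbalance rule 4.7%, and taking the smaller of the two p-values 7.1%.

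**The case against.** **The plan is valid and consistent with itself.** The sample size and the analysis both target the difference in change, so a less efficient method is not an error. This stands. The point is an improvement that costs nothing, and it does not correct a wrong result.

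**The article states no data-driven rule.** It contains no baseline significance test and no covariate selection step. The phrase could mean that the baseline value is always adjusted for because chance imbalance exists, and an analysis plan not shown may fix the covariates. This also stands: selection after seeing the groups is one natural reading, not an explicit instruction. But the kinder reading does not rescue precision. In a model that keeps baseline as a free outcome level, adding it as a covariate leaves the MHQ contrast where it was (step 2).

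**The open choice need not inflate type I error.** A strict imbalance rule did not. Inflation to about 7% needed the more favourable result to be chosen on purpose, and nothing in the article suggests that intent.

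**A stronger reading to resist.** A reader might infer that having baseline on both sides of the model halves the treatment effect, since simulation can produce about 6.5 for a true 13. That figure is the group main effect averaged over baseline and follow-up in a model without a group-by-time term. It arises with or without the baseline covariate, and it is not the quantity that {20a} targets. The group-by-time contrast is unbiased.

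**Baseline as an outcome level is not itself a fault.** With baseline means constrained equal, such a model is about as efficient as ANCOVA. The loss comes from leaving those means unconstrained.

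**Conclusion.** The point holds as a matter of precision and pre-specification. As written, the primary MHQ comparison amounts to a change-score analysis, and the imbalance clause neither regains the lost precision nor settles in advance how baseline is handled. At r = 0.66 and a change SD of about 16, ANCOVA would raise power at 24 per group from about 79% to about 85-86%.

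The direction is certain for any r below 1 under equal variances at the two visits. The size is not: it rests on an SD back-solved from the stated sample size and on a test-retest coefficient standing in for a 3-month correlation. At r = 0.9 the gain is only about 2 points.

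The documents do not support a claim of bias in the planned contrast, or a claim that covariates will definitely be picked from the observed data.

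**What to change.** In {20a}, replace the imbalance clause with wording such as:

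> The baseline value of each outcome is adjusted for in all models, whatever the observed imbalance. The primary analysis is ANCOVA of 3-month MHQ on group and baseline MHQ. Any model adjusted for other covariates is a sensitivity analysis.

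If the sponsor prefers to keep baseline as an outcome level, the near-equivalent primary analysis is a repeated-measures model with group-by-time terms and the baseline means of the two groups constrained equal. One of the two should be named.

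**Cost.** Analysis wording only. Baseline MHQ is already scheduled, and neither sample size nor visits change. The article says that any protocol change goes to the ethics committee ({25}). Recruitment was still open and no interim analysis is planned, so the change can be made cleanly, provided that it is fixed and dated before outcome data are analysed.
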